| Study Center(s)                       | Single Center                                                                                                                                                                                                                                  |
| Primary Objective                     | The primary end-point of the study is to determine the sensitivity of SGM-101 in identifying lung nodules when excited by a near-infrared light source.                                                                                        |
| Secondary Objective                   | The secondary objective is to measure the concordance of fluorescence and tumor type.                                                                                                                                                          |
| Number of Subjects                    | We intend to enroll 20 lung cancer subjects in this study.                                                                                                                                                                                     |
| Diagnosis and Main Inclusion Criteria | The study is focusing on subjects presenting with suspected malignancies of the lung and pleura who are considered to be good surgical candidates.                                                                                             |
| Study Product, Dose, Route, Regimen   | SGM-101 is a fluorescent conjugate comprised of a tumor-specific, anti-carcinoembryonic antigen (CEA) monoclonal antibody and a near infrared (NIR) emitting fluorochrome. We will give 5 to 10 mg intravenously 3 to 5 days prior to surgery. |
| Duration of administration            | The proposed dose of SGM-101 to be investigated in this study is 10 mg to be administered intravenously over 30-60 minutes.                                                                                                                    |
| Reference                             | Non-placebo controlled                                                                                                                                                                                                                         |

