### 1.1 Background

According to the World Health Organization, lung cancer is the most common cause of cancer-related death in men and women, and is responsible for 1.5 million deaths worldwide annually as of 2017. Surgery remains the best option for subjects presenting with operable Stage I or II cancers, however the five-year survival rate for these candidates remains at a dismal 73% for Stage I and 53% for Stage II (1). The high rates of local recurrence suggest that surgeons are unable to completely detect and remove primary tumor nodules in a satisfactory manner as well as lingering metastases in sentinel lymph nodes. By ensuring a negative margin through imaging during surgery it would be possible for us to improve the rates of recurrence free subjects and thus overall survival.

Over the last several years, our group has taken a novel approach to the surgical approach (2-5). Specifically, we have started injecting contrast agents that go selectively to tumors and allow them to fluoresce. We postulate that provides an additional tool in the operating room for surgeons to find tumors and their margins.

Thoracic malignancies are the ideal disease to investigate intra-operative imaging. Over 25-65% of lung and pleural malignancies express carcinoembryonic antigen (CEA), therefore making CEA a target for imaging agents (6-11). Interestingly, there is minimal expression of CEA in normal lung, therefore, the background to noise of CEA in cancers versus normal lung is very high. Unfortunately, unlike colorectal cancer, it is not evident that serum CEA levels correlate with lung cancer, specifically non-small cell lung cancer.

CEA is a glycoprotein product of the gene CEACAM-5 and is a member of the immunoglobulin superfamily that serves as a cell-adhesion molecule and may also have an effect on innate immunity. High serum CEA levels have been identified as a prognostic factor in both resected NSCLC and in metastatic disease (6, 7, 11-13).

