## **2 Study Objectives**

### **Primary Objective**

The primary study objectives are to assess the sensitivity and specificity of SGM-101 in detecting non-small cell lung carcinomas during surgery.

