### 3 Study Design

#### 3.1 General Design

Subjects will be seen in a General Thoracic Surgery clinic. If they have a lung nodule that is suspicious for a lung non-small cell lung cancer, they will be a candidate for the operation. From our prior experience, we have an 90% positive predictive value based on CAT and PET scans that a subject with a suspected lung cancer will in fact have lung cancer. The subjects with lung and pleural nodules will be prospectively consented to participate in this trial. There will be no randomization or control group and only subjects previously scheduled to undergo surgery will be eligible to participate. We anticipate a 24-month period will be necessary to reach our accrual goal of 20 subjects.

After obtaining informed consent, subjects will receive a one-time dose of 5 to 10 mg of SGM-101, up to 5 days prior to the planned operation. As a prophylactic measure, we may recommend giving 25 mg of IV Benadryl to the subject prior to the infusion of SGM-101 to ensure possibility of allergic reaction is absolutely minimized. This will be at the discretion of the principal investigator. The goal of surgery in subjects is to remove the nodule and lymph nodes in concern. During surgery, we will take images with an intra-operative camera system. Imaging will take place prior to surgical resection to record the localization of tumors, and post-resection to document the visualization of any residual tumor. All documenting of nodules will take place in an electronic report form.

Our analysis will be the following:

| Data Analysis of a Diagnostic Test |                    | Test result                                        |                                                   | Data Analysis                                                             |
|------------------------------------|--------------------|----------------------------------------------------|---------------------------------------------------|---------------------------------------------------------------------------|
|                                    |                    | True
(accept $H_0$ )                            | False
(accept $H_A$ )                          |                                                                           |

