The sensitivity will be based on the single lung nodule that is being removed in a patient. Typically for lung cancer surgery, we are there to remove one nodule. That will be the basis of the calculations. Thus, the denominator will be 10 patients for the first Cohort, and another 10 patients for the second Cohort. (A total of 20 data points for the whole study). The calculations will be based on two pieces of data: tumor fluorescence and pathology. We will not be doing a detailed IHC study at this time.

If successful, we will consider 10 more subjects. Then, with 20 subjects, we will have 90% power to identify any unforeseen adverse event that occurs with a prevalence of at least 5%. We will use a Bayesian continuous safety monitoring design that registers a signal if the posterior probability that the chance of an adverse reaction is greater than 0.1 exceeds 80%. If we encounter a safety signal, we will suspend enrollment until the issue has been addressed.

The fraction of tumors on pathology that are identified by the imaging procedure will provide an estimate of the sensitivity of the procedure. Of the 20 enrolled subjects, we expect approximately 60%, or 12, to have fluorescent tumors. With 12 tumors, an exact 95% confidence interval for sensitivity would range from (0%, 12%) if no tumors are detected up to (88%, 100%) if all 12 are detected. We will compute estimates of the sensitivity (fraction of path-positive margins that are called correctly) and specificity (fraction of path-negative margins that are called correctly), and calculate 95% confidence intervals around them. A second aim will be to estimate the sensitivity of the procedure for identifying all lesions, including lesions that were not pre-identified. Because some subjects will contribute more than one lesion, we will estimate these parameters using random effects logistic regression models (in SAS Proc Glimmix) that allow for between-subject variability. These specimens will provide independent estimates of the positive and negative predictive values of discovering satellite nodules.

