## 7.2 Statistical Methods

All data will be summarized, with means and standard deviations for continuous variables and proportions for categorical variables. Graphical techniques will be used for data exploration. Analyses will be primarily descriptive. The remainder of the statistical approaches is described above.

Null hypothesis = Lung cancers will not fluoresce with a CEA-targeted dye.

Alternative hypothesis = Lung cancers will fluoresce with a CEA-targeted dye.

Alpha = 0.25

Beta = 0.5

There are 20 patients, thus the denominator will be 20.

Each patient will contribute one nodule or cancer to the study.

Patients with more than one nodule typically do not get surgery because that represents metastatic disease and is considered non-surgical.

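### Sections 7.1 and 7.2 base sensitivity on 20 patients and on 12 fluorescent tumors, but the protocol's own definition calls for pathology-confirmed cancers (about 18 expected); specificity then rests on about 2 nodules

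*Protocol*

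**What the plan says.** **Definition.** Sections 3.1 and 7.1 print the same two-by-two table, with sensitivity = TP/(TP+FN) and specificity = TN/(TN+FP). A false negative is a cancer that does not fluoresce; a true negative is a non-cancer that does not fluoresce. Section 7.1 also describes sensitivity in words as the share of tumors on pathology that imaging finds.

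**Denominator of 20.** Section 7.1 bases the calculation on one nodule per patient and says "the denominator will be 10 patients for the first Cohort, and another 10 patients for the second Cohort", adding "A total of 20 data points for the whole study". Section 7.2 repeats it: "There are 20 patients, thus the denominator will be 20".

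**Base of 12.** For precision, Section 7.1 says "Of the 20 enrolled subjects, we expect approximately 60%, or 12, to have fluorescent tumors". It then gives exact 95% intervals for sensitivity on 12 tumors: 0-12% if none is detected and 88-100% if all are.

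**Margins.** The next sentence of Section 7.1 defines sensitivity and specificity as the fractions of pathology-positive and pathology-negative margins called correctly.

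**Population.** Section 3.1 states, for suspected lung cancer, "we have an 90% positive predictive value based on CAT and PET scans". Section 4.1 admits subjects with a resectable lung or pleural nodule or mass and does not require confirmed cancer. The Study Summary says "We intend to enroll 20 lung cancer subjects in this study".

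**Objectives.** Section 2: "The primary study objectives are to assess the sensitivity and specificity of SGM-101 in detecting non-small cell lung carcinomas during surgery". The primary objective row of the Study Summary names sensitivity alone.

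**The concern.** One estimate has four descriptions: pathology-confirmed cancers, all 20 patients, 12 fluorescent tumors, and margins. The first is the correct one. The others are not harmless variants of it.

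- A denominator of 20 puts benign nodules in with the cancers. A benign nodule that correctly stays dark then lowers the reported sensitivity.
- The 12 are described by the test result. They are expected true positives, so as a base for sensitivity they leave out the false negatives.
- Margins are a different unit, and the number available is not given.

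This is the main result of the study. An analyst who follows Section 7.2 and one who follows the table would report different sensitivities from the same data. Specificity is named as primary in Section 2, but the number of benign nodules that would support it is never worked out.

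**Working it through.** **Inputs**
- Patients and index nodules: 20, one each (Sections 7.1 and 7.2).
- Probability that a suspected lung cancer is cancer: 0.90 (Section 3.1).
- Expected fluorescent tumors: 12 (Section 7.1).
- Interval: exact two-sided 95% (Study Summary and Section 7.1), taken as Clopper-Pearson. For 0/n the upper limit is 1 − 0.025^(1/n); for n/n the lower limit is 0.025^(1/n).

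**Step 1. The plan's own figures**
- 0.60 × 20 = 12. This reproduces.
- 0/12: upper limit 1 − 0.025^(1/12) = 26.5%. The protocol gives 12%.
- 12/12: lower limit 0.025^(1/12) = 73.5%. The protocol gives 88%.
- Other methods for 0/12 do not give 12% either: one-sided 95% gives 22.1%, Wilson 24.3%, the rule of three 25%.
- A two-sided exact upper limit that rounds to 12% needs n of 28 to 30. The printed interval therefore fits none of 12, 18 or 20.

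**Step 2. Expected denominators under the protocol's definition**
- Cancers (TP+FN): 20 × 0.90 = 18.
- Non-cancers (TN+FP): 20 × 0.10 = 2.

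**Step 3. Effect on sensitivity if 12 cancers fluoresce**

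| Denominator | Estimate | Exact 95% CI |
|---|---|---|
| 20 patients (7.1, 7.2) | 12/20 = 60.0% | 36.1-80.9% |
| 18 cancers (definition) | 12/18 = 66.7% | 41.0-86.7% |

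If all 18 cancers fluoresce, dividing by 20 gives 18/20 = 90%, the highest value that rule allows.

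**Step 4. Precision on the expected 18 cancers**
- 0/18: 0 to 1 − 0.025^(1/18) = 0-18.5%.
- 18/18: 0.025^(1/18) to 100% = 81.5-100%.

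**Step 5. Specificity on about 2 non-cancers**
- 2/2: 15.8-100%. 1/2: 1.3-98.7%. 0/2: 0-84.2%.
- Chance of no benign index nodule at all: 0.90^20 = 12.2%.
- Chance of 3 or fewer: 86.7% (binomial, 20 nodules, probability 0.10).

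**Step 6. Range for the 90% (80% and 95% are assumed alternatives)**

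| Probability of cancer | Cancers | Non-cancers | 12 detected / cancers | Ceiling if divided by 20 |
|---|---|---|---|---|
| 80% | 16 | 4 | 12/16 = 75% | 80% |
| 90% | 18 | 2 | 12/18 = 67% | 90% |
| 95% | 19 | 1 | 12/19 = 63% | 95% |

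The estimate from Section 7.2 is 60% in every row.

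**The case against.** **The correct estimator is already in the protocol.** It is, in the table, the cell definitions and one sentence of Section 7.1. So the plan does not lack a definition of sensitivity. It has a correct one beside explicit instructions that contradict it, and those instructions are the ones that fix the denominator.

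**Twenty is right if all 20 have lung cancer.** The Study Summary can be read that way. But Section 4.1 does not require cancer and Section 3.1 expects one suspected case in ten not to be cancer. If all 20 did have cancer, specificity on the index nodule would have no denominator.

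**Eighteen is only an expectation.** This stands. The 90% refers to suspected lung cancer on imaging. Eligibility is wider, since pleural nodules are allowed, and the objective is narrower, since it names non-small cell carcinoma. The count could be below 18 if only that histology counts.

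**The study is a pilot with descriptive analyses, and exact intervals for both measures are already planned in the Study Summary.** This is true and it lowers the demand for precision. It does not change which nodules belong in the denominator.

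**Stronger readings that the documents do not support**
- A reader might infer that the plan makes sensitivity 100% by construction, because 12 fluorescent tumors would be divided by 12. The 12 appears only in an illustration that runs from none detected to all detected. Nowhere is the final estimate said to be divided by 12.
- A reader might set the expected 12 against the Background statement "Over 25-65% of lung and pleural malignancies express carcinoembryonic antigen (CEA" and call it too high, since 65% of 18 is 11.7. The gap is 0.3 of a tumor, the range is introduced with a word that makes 65% no firm ceiling, and the 60% itself lies within it. There is no inconsistency.
- A reader might conclude that specificity cannot be estimated. It can, unless no benign nodule occurs; it would be extremely imprecise.

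**Conclusion.** The point holds. Sections 7.1 and 7.2 contradict the protocol's definition of sensitivity: the stated denominator of 20 is the number of patients, the planning base of 12 is the expected number of true positives, and the margin sentence changes the unit.

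Under the protocol's own 90%, dividing by 20 understates sensitivity by about 7 percentage points if 12 cancers fluoresce and by 10 points for a perfect agent. Under assumed probabilities of 80% to 95% the first figure runs from 15 to 3 points. These sizes rest on one index nodule per patient and on the 90% applying to those enrolled.

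The printed precision is wrong whatever denominator is chosen among 12, 18 and 20. At the extremes it claims a width of 12 points, against 26.5 for 12 tumors and 18.5 for 18.

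Specificity, with about 2 expected non-cancers, would be almost uninformative on the index nodule. Section 2 and the objective row of the Study Summary also disagree on whether it is primary. This part carries less weight than the denominator conflict.

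**What to change.** 1. In Sections 7.1 and 7.2, state that the denominator for sensitivity is the index nodules with pathology-confirmed cancer and that for specificity the index nodules without cancer. Say whether cancer here means any malignancy or only non-small cell carcinoma, since the table and Section 2 differ.
2. Delete 20 and 12 as denominators. Keep 20 as the number of patients and 12, if wanted, as an expected number of detections.
3. Remove the margin-based definitions from the primary estimate. If margins are of interest, list them as a separate exploratory analysis.
4. Replace the printed intervals with those for about 18 cancers: 0-18.5% if none is detected and 81.5-100% if all are. Say that 18 is an expectation and give the range of 16 to 19.
5. Reconcile Section 2 with the Study Summary. The simplest course is sensitivity as the primary endpoint and specificity as a descriptive count with its exact interval, noting that about 2 non-cancers are expected.
6. In the Study Summary, describe the 20 as having suspected lung cancer.

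The cost is a wording amendment; procedures and sample size do not change. The sponsor gives up a favourable precision statement and any firm claim about specificity, neither of which the design supports.

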| Statistical Methodology               | The sensitivity and specificity of the intra-operative imaging will be estimated using microscopic pathological examination as the gold standard. Exact 95% confidence intervals will be generated around these estimates.                     |

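### The exact 95% limits given for sensitivity with 12 tumors are wrong: they should be (0%, 26%) and (74%, 100%), so precision at 12 tumors is overstated more than twofold

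*Protocol*

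**What the plan says.** The Protocol's Study Summary names sensitivity as the primary endpoint. For the estimates of sensitivity and specificity it specifies the interval method: "Exact 95% confidence intervals will be generated around these estimates".

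Section 7.1 (Sample Size Determination) then gives the planned precision. It sets the number of tumors first: "Of the 20 enrolled subjects, we expect approximately 60%, or 12, to have fluorescent tumors". On that number it states the interval for the two extreme results: "exact 95% confidence interval for sensitivity would range from (0%, 12%) if no tumors are detected up to (88%, 100%) if all 12".

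Two other statements bear on the denominator. Section 7.2 says "There are 20 patients, thus the denominator will be 20". Section 3.1 says of preoperative imaging in suspected lung cancer that "we have an 90% positive predictive value based on CAT and PET scans", which implies about 18 cancers among 20 subjects.

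**The concern.** The sentence fixes everything needed to compute the limits: the method (exact), the confidence level (95%), the denominator (12) and the outcomes (0/12 and 12/12). The printed limits look far too tight for 12 observations. Even the rule of three, 3/n, puts the upper limit at 0/12 near 25%.

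Section 7.2 describes the analyses as mainly descriptive, so interval width is the natural measure of what this trial can show about sensitivity. This is the only place where the protocol puts a number on it. It quotes only the two outcomes at which the interval is narrowest, and both are stated too favourably. Anyone judging whether 20 subjects can answer the primary question would be working from a wrong figure.

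**Working it through.** **Inputs.** n = 12 tumors, exact method, 95% level, outcomes 0/12 and 12/12 (all section 7.1). The Study Summary confirms the exact method and the 95% level.

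**Exact (Clopper-Pearson) limits at the extremes.**
- Upper limit at 0/n = 1 − 0.025^(1/n). For n = 12: 1 − 0.7354 = 0.2646, so the interval is (0%, 26.5%).
- Lower limit at n/n = 0.025^(1/n). For n = 12: 0.7354, so the interval is (73.5%, 100%).
- Check: 0.7354^12 = 0.025, as required.
- Width: 26.5 points against the stated 12, and 26.46/12 = 2.2. If the stated 12% is itself rounded from somewhere between 11.5% and 12.5%, the ratio is between 26.46/12.5 = 2.1 and 26.46/11.5 = 2.3.

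**Attempts to reproduce the printed 12%.** Upper limit at zero detected:

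| Reading | Upper limit |
|---|---|
| n = 12, exact two-sided 95% | 26.5% |
| n = 12, exact one-sided 95%: 1 − 0.05^(1/12) | 22.1% |
| n = 12, mid-P | 22.1% |
| n = 12, Wilson | 24.2% |
| n = 12, Agresti-Coull | 28.2% |
| n = 12, Sterne | 24.3% |
| n = 12, Blaker | 23.5% |
| n = 12, Jeffreys | 18.5% |
| n = 12, rule of three: 3/12 | 25% |
| n = 18, exact two-sided 95% | 18.5% |
| n = 20, exact two-sided 95% | 16.8% |
| n = 20, Jeffreys | 11.7% |

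Only the last row comes close. It is neither an exact interval nor based on 12 tumors, so it contradicts the sentence on both counts.

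**What a 12% limit would require.**
- Confidence actually attached to it at n = 12: the tail is 0.88^12 = 0.216, so the two-sided confidence is 1 − 2 × 0.216 = 57% and the one-sided confidence is 78%.
- Tumors needed for an exact two-sided limit of 12%: ln(0.025)/ln(0.88) = 28.9, about 29. Allowing for rounding, 28 to 30 tumors give a limit that prints as 12%.
- Tumors needed on a one-sided reading: ln(0.05)/ln(0.88) = 23.4, so 23 to 24.
- Both exceed the 20 subjects planned.

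**Mid-range outcomes, which the protocol does not show.** At 6/12 the exact interval is (21.1%, 78.9%), 58 points wide.

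**The same limits on the expected number of cancers.** Applying the 90% predictive value in section 3.1 to 20 subjects gives 0.9 × 20 = 18. Exact intervals: 0/18 (0%, 19%); 9/18 (26%, 74%); 12/18 (41%, 87%); 18/18 (81%, 100%).

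**The case against.** The arithmetic has no defence. The two printed limits are complements (12 and 88) in running text, so faulty text extraction is not a plausible explanation, and no other section corrects them. What can be argued is how much the error matters.

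The trial is labelled pilot and exploratory. The 20 subjects are not derived from this interval, and no enrolment, stopping or success rule uses it; the decision after the first cohort rests on false positives. The reported interval will be computed from the data by the exact method, so the wrong planning figure will not carry into the results. All of this is true and limits the harm to the planning stage. It does not remove it: a pilot may be imprecise, but the precision it states should be correct, and no other number in the protocol describes precision for the primary endpoint.

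The size of the overstatement also depends on the reading. The ratio of 2.2 applies to 12 tumors and a two-sided interval. It is 22.1/12 = 1.8 on a one-sided reading, 18.5/12 = 1.5 with 18 cancers, and 16.8/12 = 1.4 with the denominator of 20 given in section 7.2. That qualification stands, but the sentence itself specifies 12 tumors and a 95% interval with no one-sided qualifier, and the printed limits are too narrow on every one of these readings.

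Finally, the protocol makes no claim about mid-range results, so leaving them out is a weakness of presentation and not an error.

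**Conclusion.** The limits are wrong as written. For 12 tumors the exact two-sided 95% intervals are (0%, 26%) and (74%, 100%), so the stated width of 12 points should be 26.5, an overstatement of precision by a factor of 2.2. A result of 12/12 would exclude sensitivity below about 74%, not below 88%.

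This rests on nothing beyond what section 7.1 states, with exact taken as Clopper-Pearson. The other methods and denominators tried do not rescue the sentence. The figures for 18 cancers are additional and assume that the 90% predictive value in section 3.1 applies to the enrolled subjects; the core correction does not depend on them.

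Because this is the only numerical precision statement for the primary endpoint, it must be corrected.

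**What to change.** In section 7.1, replace the two intervals for 12 tumors with (0%, 26%) if none and (74%, 100%) if all 12 are detected, and add a mid-range case, for example 6/12 giving (21%, 79%).

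A useful further step is to restate precision on the expected number of pathology-confirmed cancers, since section 3.1 defines sensitivity as TP/(TP + FN) with cancer on pathology as the reference, whereas section 7.1 introduces 12 as the number of fluorescent tumors. With about 18 cancers (90% of 20, stated as an assumption) the exact intervals are (0%, 19%) at 0/18, (26%, 74%) at 9/18, (41%, 87%) at 12/18 and (81%, 100%) at 18/18. If this is done, one denominator should be used throughout and its source given, because section 7.2 currently gives 20.

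The cost is one sentence for the minimum correction. The stated precision becomes less favourable; enrolment, procedures and the planned analysis do not change.
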